## Abstract

**Background:**

The effect of pretravel health advice (PTHA) on travel-related illness rates is poorly understood, and to date there are no published randomized controlled trials evaluating the impact of PTHA outcomes.

**Objective:**

This study aims to determine the effect of an online PTHA intervention on travel-related illness rates in Western Australians visiting Bali, Indonesia.

**Methods:**

Western Australian travelers to Bali will be recruited online before departure and will be randomly allocated to an intervention or control group by computer algorithm. The intervention in this study is a short animated video, with accompanying text, containing PTHA relevant to Bali. An online posttravel survey will be administered to all participants within two weeks of their return from Bali. The primary outcome is the difference in self-reported travel-related illness rates between control and intervention groups. Secondary outcomes include the difference in risk prevention behaviors and health risk knowledge between the control and intervention groups. Further secondary outcomes include whether individuals in the control group who sought external PTHA differ from those who did not with respect to risk prevention behaviors, health risk knowledge, and health risk perception, as well as the rate of self-reported travel-related illness.

**Results:**

The study began recruitment in September 2016 and will conclude in September 2017. Data analysis will take place in late 2017, with results disseminated via peer-reviewed journals in early 2018.

**Conclusions:**

This will be the first randomized controlled trial to examine the effect of a novel PTHA intervention upon travel-related illness. In addition, this study builds upon the limited existing data on the effectiveness of PTHA on travel-related illness.

**ClinicalTrial:**

Australian New Zealand Clinical Trials Registry (ANZCTR): ACTRN12615001230549; https://www.anzctr.org.au/Trial/Registration/TrialReview.aspx?id=369567 (Archived by WebCite at http://www.webcitation.org/6m0G7xJg1)

## Introduction

### Australian Travel Overseas

Increasing numbers of Australians are traveling overseas. The number of short-term international departures from Australia doubled to over 9.4 million in 2015, compared to the previous 10 years [1].

Bali, Indonesia has been a popular holiday destination for Australians since the 1970s. Western Australian (WA) travelers now account for nearly half of the total Australian visitors to Indonesia, increasing more than six-fold between 2006 and 2015 [1]. There were over 454,000 departures from Perth to Bali in 2015, with nine flights, on average, every day [2]. Travelers from Perth to Bali are the focus of our study.

### Rates of Travel-Related Disease in Returning Travelers

Reported rates of travel-related illness vary, with studies estimating that 22-64% of travelers experience some form of health impairment while traveling, depending on the destination and season of travel [3]. In Western Australia, almost 8% of communicable disease notifications are for illnesses acquired overseas. From 2006 to 2015, the proportion of overseas-acquired infections in Western Australia attributed to travel to Indonesia rose from 10% to 42% (personal communication from [name], Data Custodian for the Western Australian Notifiable Infectious Diseases Database at the Western Australian Department of Health, April 7, 2016) [4]. The most common notifiable diseases acquired in Indonesia are dengue fever and gastroenteritis caused by *Campylobacter* and *Salmonella* species [4].

Establishing an accurate picture of travel-related infections is difficult due to underdiagnosis and under-reporting, the highly transient nature of international travel, and the emergence of new disease risks in travel destinations. In particular, while notifiable disease data are available, there are no comparable data available for non-notifiable illnesses, such as traveler’s diarrhea, among residents returning to Western Australia.

### Pretravel Health Advice in Travelers

Delivering appropriate and effective pretravel health advice (PTHA) to travelers may be important to reduce the risk of illness to travelers and to prevent the importation of travel-related diseases [5]. The average proportion of travelers seeking professional PTHA globally, as reported in airport surveys, is approximately 48% [5]. Travelers from the United States, Australia, and Asia are reported to consistently fall below this average [6-9], with Canadian and European travelers reporting PTHA more frequently [10-12].

### Outcomes of Pretravel Health Advice: Rate of Illness

There are limited and conflicting data on the impact of PTHA in reducing travel-related illnesses. A retrospective cohort study in Scotland found that people who consulted a travel doctor prior to traveling overseas were less likely to become ill than those who had seen a general practitioner [13]. However, of the 1668 participants, only 100 had attended a travel clinic. An Italian retrospective study of 300 travelers to malaria-endemic countries showed that visiting a travel clinic pretravel was protective against travelers’ diarrhea, but not against fever [14]. In an analysis of European surveillance data, travelers falling ill abroad were less likely to present with malaria, acute hepatitis, HIV, or animal bites requiring postexposure prophylaxis if they had received PTHA [15].

Conversely, some researchers have concluded that PTHA does not protect against illness in travelers [16-19]. It is proposed that people who take advice prior to travel may already be more aware of travel illnesses, possibly due to previous exposure or personal susceptibility [16,17]. In a recent prospective cohort study of 1277 patients at a Swedish travel clinic, illness after travel was compared between those who complied with the advice and those reporting noncompliance or inattention to PTHA provided [19]. Self-reported compliance with PTHA was not found to be protective against illness while travelling.

The observational studies cited above demonstrate discordant results regarding the effect of PTHA on reducing travel-related illness. However, methodological issues such as selection bias and sample size limit the inferences that can be drawn from these studies. To address these issues, our proposed study incorporates a randomized controlled trial design on a large cohort to evaluate the effect PTHA has on reported illness. Specifically, the aim of the study is to determine the effect of an online PTHA intervention on travel-related illness rates and behaviors in WA travelers visiting Bali, Indonesia.

## Methods

### Study Design

To evaluate the impact of PTHA on travel-related illness, rates of self-reported illness in travelers with and without PTHA will be compared (see Figure 1).

**Figure 1 figure1:**
[figure not shown]
Pretravel health advice (PTHA) among Australians returning from Bali, Indonesia: study design and flow.

#### Study Population

WA residents planning to travel to Bali within a 12-month study period commencing in September 2016 will be eligible for inclusion in this study. Participants must be Australian residents, over the age of 18, traveling to Bali and staying for at least one night, and be willing and able to give consent and agree to complete the survey.

#### Recruitment

Recruitment will take place online, via advertisements promoting the Bali travel survey, strategically located on Facebook and Google pages. The advertisements will run for a 12-month study period to incorporate variation in travel across the year related to seasonal travel or university and school holidays. The advertisements will target people who have searched for Bali flights and/or accommodation online; this information is gathered by Facebook and Google through their single sign-on utility, as well as cookie data to track Internet activity. The main avenue for recruitment is the Internet because a previous study demonstrated that 87% of travelers to Bali make pretravel purchases—flights or accommodation—online [20]. Clicking on the advertisement will take people to a webpage, which briefly describes the study. People interested in enrolling in the study will be asked to enter their departure date, return date, sex, age range, and email address in an online form. This information will allow researchers to determine the age range and sex of those participants who later may be lost to follow-up. Participants will be asked to check a box to indicate that they consent to participate in the study. Travelers can only participate once in the study; multiple enrollments from the same email address will be blocked.

To assist with recruitment, participants will be offered an incentive of entering a lottery to win one AUD $1000 gift voucher or one of 10 AUD $100 gift vouchers. The winning names will be drawn upon study completion. Participants will be informed of the incentive via the online advertisement, consent page, and initial welcome email they receive.

#### Randomization

Randomization will be performed using a custom-built computer algorithm. Participants will be randomly allocated into control or intervention groups after completion of the online enrollment form, and the allocation will be sent to the email management program (MailChimp) used in the study. A block randomization (block size=4) with a uniform 1:1 allocation will be used.

#### Intervention

All participants will receive an email following enrollment containing a welcome message and a reminder to look for an email within two weeks of their return date. For participants allocated to the intervention group, this email will contain the link to the PTHA intervention.

The intervention in this study is a short, approximately 3-minute, online animated video containing PTHA specific to Bali and Southeast Asia. Topics covered include foodborne illness (eg, Bali belly), mosquito-borne illness (eg, dengue, chikungunya, and Zika), avoiding monkey and canine contact (eg, rabies), and checking measles vaccination status. This video is complemented by PTHA in text below the video and the webpage is optimized for mobile devices. This intervention was developed in consultation with a video producer who has previously created videos for the WA Department of Health. The information in the video and text was developed from a review of the travel-related illness literature, as well as reputable websites such as the Australian government smartraveller.org website [21]. This website was the only PTHA source that showed higher levels of health knowledge among travelers to Bali participating in an airport survey in 2014 [20]. The video producers will provide a *video heat map* that graphs each viewing session (ie, where and when the video was watched, which portions were skipped or watched again, and the percentage of the video that each participant watched). The participant may view the video multiple times, accessing it through the email link. The control group will not receive access to this PTHA video, but they may access PTHA on their own accord.

#### Posttravel Follow-Up

Within two weeks of the participants’ nominated return dates, they will receive an email containing a link to the posttravel survey, which will be optimized for mobile devices. The control and intervention groups will receive links to surveys that are almost identical, apart from the wording of one question on PTHA. For the intervention group, this question will be phrased to make it clear they are being asked about PTHA received external to this study (ie, PTHA from their general practitioner or from their own Internet search). If the participant does not complete the survey within a week, a second email will be sent to the participant.

The survey will contain questions in six general themes: (1) information about their trip to Bali, (2) PTHA behaviors, (3) risk prevention behaviors (sample question presented in Textbox 1), (4) knowledge about disease risk (sample question presented in Textbox 2), (5) illness and symptoms during and/or posttravel, and (6) basic demographic information. The survey was adapted from a 2014 WA traveler survey [20] and will take participants, on average, between 5 and 10 minutes to complete, depending on whether or not illness is reported. The final survey and intervention were developed in consultation with WA Department of Health staff and pilot-tested, with the intervention, by a focus group in late 2015.

Posttravel survey sample questions. Participants will be asked to report the health risk-prevention behaviors they engaged in during travel. Participants may choose from the following responses: Daily, Every 2-3 days, Once a week, and Never.Please answer the following questions about your behavior during your recent trip to Bali.How often did you use insect repellent on this trip?How often did you use alcohol-based hand sanitizer on this trip?How often did you use a mosquito net on this trip?How often did you use mosquito protective clothing on this trip? (eg, long sleeves)How often did you eat eggs with a runny yolk on this trip? (eg, fried egg on top of fried rice)How often did you eat fresh fruit you did not peel yourself on this trip?

Posttravel survey sample questions. Participants will be asked to report their health risk knowledge posttravel. Participants may choose from the following responses: Agree, Disagree, and Unsure.The following questions concern your opinions on health risks while traveling.Please indicate whether you agree or disagree with each of the statements by ticking the appropriate box.The risk of someone catching measles in Bali is about the same as catching measles in Australia.Mosquitoes that bite during the daytime are a nuisance, but they do not transmit serious diseases.The ice from hotels in Bali is safe to serve in drinks.It is safe to feed monkeys at tourist venues in Bali.Salads (ie, uncooked fruits and vegetables) are safe to eat in Bali.You should seek urgent medical attention if you are bitten by a dog or other mammal in Bali.It is important to always use insect repellent when outdoors in Bali.If you are scratched or bitten by a monkey in Bali, you should receive treatment to prevent rabies.You should not eat eggs with runny yolks in Bali.

Participants who report seeking medical attention for a travel-related infection will be asked for permission to obtain specified health information relating to their illness from their health care provider. If consent is given, the participant will be asked to provide some identifying information including name, date of birth, name of medical practice or hospital visited, and the date of medical visit. Participants are advised that the information to be collected from the health care provider will include details regarding relevant diagnosis, laboratory tests, prescriptions, and, if admitted, length of stay. Letters will be sent to health care providers informing them that the participant has consented to participate in the study and that a WA Department of Health employee will contact them within the week by telephone. The WA Department of Health employee will conduct a phone interview with the health care provider using a uniform script. The self-reported data on diagnoses, health services accessed, and treatment will be validated against the health records.

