#### Sample Size Calculation

The sample size calculation was based upon the online PTHA intervention lowering the rate of self-reported illness in Western Australians returning from Bali by 10%. Existing literature suggests that reduction in illness as a result of visiting a travel doctor before departure is approximately 20% [13,14]. The sample size calculation assumed an illness rate of 40% in the control group [3], with a reduction of 10% in the intervention group, detected at 80% power with a *P* value of .05. A sample size of 712 participants completing the study—356 control and 356 intervention participants—was determined using PS: Power and Sample Size Calculation statistical software [25]. Assuming approximately 50% of participants are lost at follow-up, which is the average for Internet-based trials [26], and although we expect less loss because of the incentive, at least 1424 participants—712 exposed and 712 unexposed participants—would need to be enrolled in the study.

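### One reminder email is the only follow-up described for a survey that is the sole source of the primary outcome; further reminders would be a cheap guard against attrition bias and a response shortfall

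*Protocol article*

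**What the plan says.** Under Posttravel Follow-Up, an email with the survey link is sent within two weeks of the nominated return date. The next step is: "If the participant does not complete the survey within a week, a second email will be sent to the participant". No later contact is described.

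The survey carries the questions on illness during and after travel, so a person who does not answer has no primary outcome. Provider records are sought only for people who report in the survey that they sought care, and they serve to validate those reports.

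Under Sample Size Calculation, the plan takes "Assuming approximately 50% of participants are lost at follow-up, which is the average for Internet-based trials" and enrolls at least 1424 to obtain 712 completers. The same sentence adds that the authors expect to do better than this because of the incentive.

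Other measures support retention. There is a prize draw (Recruitment), a welcome email that tells participants to expect the survey (Intervention), and a short survey optimized for mobile devices (Posttravel Follow-Up). Age range and sex are recorded at enrollment so that those lost can be described. The primary analysis is stated to be by intention to treat.

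**The concern.** When up to half of the randomized participants may have no outcome, the comparison depends on who chose to answer. Doubling enrollment replaces the missing numbers but leaves the selection as it was.

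Selective response is plausible here. Only the intervention arm is sent a link to a video about travel illness, and survey length depends on whether illness is reported, so completion could vary with both arm and outcome. Little can be repaired afterwards: the enrollment form records only travel dates, sex, age range and email address, and the other demographics come from the survey itself. Obtaining more of the outcomes is therefore the main protection, and one reminder is a light effort toward it.

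A second, smaller issue is margin. The enrollment floor meets the power target exactly at 50% response, a figure that the plan describes as an average for trials of this kind.

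**Working it through.** **Inputs.** From Sample Size Calculation: "The sample size calculation assumed an illness rate of 40% in the control group", "with a reduction of 10% in the intervention group", "detected at 80% power", significance level .05, 356 completers per arm, at least 1424 enrolled. From Randomization: allocation "with a uniform 1:1 allocation will be used". The article does not say whether the reduction is absolute or relative, or whether the test is two-sided. An absolute reduction (40% v 30%) and a two-sided test reproduce the stated number, so both are used here.

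**Step 1: reproduce the plan's figure.** With pooled proportion 0.35,

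n per arm = [1.96·√(2·0.35·0.65) + 0.8416·√(0.40·0.60 + 0.30·0.70)]² / 0.10²
= [1.96·√0.455 + 0.8416·√0.45]² / 0.01
= [1.3221 + 0.5646]² / 0.01 = 355.9, so 356 per arm and 712 in total.

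Allowing for 50% loss: 712 / 0.5 = 1424. Both match the article.

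**Step 2: power and precision by response rate, with 712 enrolled per arm.** With n = 712 × response rate,

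power = Φ[(0.10·√n − 1.96·√0.455) / √0.45]
95% CI half-width = 1.96·√(0.45 / n)

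| Response | Completers per arm | Power | Half-width (points) |
|---|---|---|---|
| 40% | 284.8 | 70.7% | 7.8 |
| 45% | 320.4 | 75.7% | 7.3 |
| 50% (planned) | 356 | 80.0% | 7.0 |
| 55% | 391.6 | 83.6% | 6.6 |
| 60% | 427.2 | 86.7% | 6.4 |

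The rows other than 50% are assumptions. The documents give neither the yield of a reminder nor a lower response scenario.

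**Step 3: attrition bias, which enrollment does not remove.** All response patterns here are assumed, for illustration.

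- Suppose there is no true effect, with 40% ill in both arms and 50% response overall. In one arm the ill respond at 55% and the well at 46.7%; in the other arm response is unrelated to illness. The first arm's observed rate is 0.40·0.55 / (0.40·0.55 + 0.60·0.467) = 0.2200 / 0.5002 = 44.0%, a spurious difference of 4 points.
- With 60% and 43.3% instead, it is 0.2400 / 0.4998 = 48.0%, a spurious difference of 8 points, against a design effect of 10.
- More generally, if illness among one arm's nonresponders differs from that among its responders by d points, that arm's observed rate is off by (fraction lost) × d. With d = 10 this is 5 points at 50% loss, 4 at 40% and 3 at 30%.

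None of these figures depends on the number enrolled. The last line shows a benefit from higher response only if d does not grow among those still missing.

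**The case against.** The strongest reply is that the plan already provides for this loss. At 50% loss power is 80.0%, 1424 is a minimum and not a cap, the authors expect better than 50%, and retention also rests on the prize draw, the advance notice and the short survey. One reminder on top of these is a defensible operational choice, and nothing in the article is miscalculated or contradictory. All of this stands. It answers the planned power but not the bias. The prize draw is also introduced as an aid to recruitment, and the article does not say whether entry depends on completing the survey.

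Several stronger readings are tempting, and the documents do not support them:

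- A reader might infer that a single reminder costs the trial planned power. It does not; extra response would add power above the target.
- A reader might infer that the authors expect to lose half the outcomes. Fifty percent is their planning value.
- A reader might infer that more reminders are certain to reduce bias. That holds only if late responders resemble the remaining nonresponders, or if the response gap between arms narrows.
- A reader might infer that reminders are fully automated and free. The article names an email management program but gives no cost and does not say how nonresponders are identified.

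The article is also condensed, and a fuller contact schedule may exist. Against that, the single reminder is a stated procedure, so it can be judged as written.

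**Conclusion.** The point holds as a low-cost design improvement and not as an error. The outcome that decides the trial has one described reminder behind it, while the plan allows for about half of those outcomes to be missing.

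The main reason to act is attrition bias. Under modest assumed selection in one arm it could reach 4 to 5 points, and under stronger selection 8 points, against a 10-point design effect. The second reason is the lack of margin at 1424 enrolled if response falls short of 50%: 75.7% power at 45% and 70.7% at 40%. Neither shortfall is predicted by the documents.

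An assumed gain of 5 to 10 points over 50% would raise power to about 84% to 87%, with a half-width of 6.6 to 6.4 points instead of 7.0. These figures rest on 40% v 30% illness, a two-sided 5% test and equal response in both arms. The gain itself is not in the documents.

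**What to change.** In Posttravel Follow-Up, schedule at least two more email reminders to nonresponders, for example two and three weeks after the first email. Use an identical timetable in both arms and link to the same full survey. Word the illness question so that it refers explicitly to the fixed window in the primary analysis (the trip and the two weeks after return), so that early and late responders report on the same period. State a survey closing date.

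A single-question link for the last reminder may look attractive, but it would measure the primary outcome with a second instrument in a self-selected late group, who would supply no behavior, knowledge, cost or external-advice data. It is better left out, or confined to a sensitivity analysis.

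The cost is two further emails through the system already in use and a short ethics notification. The downside is somewhat longer recall for late responders and a few unsubscribes. Randomization, the intervention and the analysis stay as they are.
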